# Uptake and effectiveness of a tailor-made online lifestyle programme targeting modifiable risk factors for dementia among middle-aged descendants of people with recently diagnosed dementia: study protocol of a cluster randomised controlled trial (Demin study)

**DOI:** 10.1136/bmjopen-2020-039439

**Published:** 2020-10-16

**Keywords:** dementia, risk management, epidemiology, preventive medicine, public health

## Abstract

**Introduction:**

Descendants of patients with dementia have a higher risk to develop dementia. This study aims to investigate the uptake and effectiveness of an online tailor-made lifestyle programme for dementia risk reduction (DRR) among middle-aged descendants of people with recently diagnosed late-onset dementia.

**Methods and analysis:**

Demin is a cluster randomised controlled trial, aiming to include 21 memory clinics of which 13 will be randomly allocated to the passive (poster and flyer in a waiting room) and 8 to the active recruitment strategy (additional personal invitation by members of the team of the memory clinic). We aim to recruit 378 participants (40–60 years) with a parent who is recently diagnosed with Alzheimer’s disease or vascular dementia at one of the participating memory clinics. All participants receive a dementia risk assessment (online questionnaire, physical examination and blood sample) and subsequently an online tailor-made lifestyle advice regarding protective (Mediterranean diet, low/moderate alcohol consumption and high cognitive activity) and risk factors (physical inactivity, smoking, loneliness, cardiovascular diseases (CVD), hypertension, high cholesterol, diabetes, obesity, renal dysfunction and depression) for dementia. The primary outcome is the difference in uptake between the two recruitment strategies. Secondary outcomes are change(s) in (1) the Lifestyle for Brain Health score, (2) individual health behaviours, (3) health beliefs and attitudes towards DRR and (4) compliance to the tailor-made lifestyle advice. Outcomes will be measured at 3, 6, 9 and 12 months after baseline. The effectiveness of this online tailor-made lifestyle programme will be evaluated by comparing Demin participants to a matched control group (lifelines cohort).

**Ethics and dissemination:**

This study has been approved by the Dutch Ministry of Health, Welfare and Sport according to the Population Screening Act. All participants have to give online informed consent using SMS-tan (transaction authentication number delivered via text message). Findings will be disseminated through peer-reviewed journals and (inter)national conferences.

**Trial registration number:**

NTR7434.

Strengths and limitations of this studyThis is the first multicentre trial that focuses on dementia risk reduction in middle-aged descendants of recently diagnosed patients with Alzheimer’s disease or vascular dementia.The programme gives participants insight in their risk and protective factors for dementia and provides a tailor-made online lifestyle advice with regard to 13 modifiable risk factors for dementia, taking the stages of (health behaviour) change into account.The application ensures the privacy of the participants by using SMS-tan for logging in their personal account and signing the electronic informed consent form.The web-based application (demin.nl) functions fully automatically, making it easy to implement the study in other memory clinics and settings.Changing health behaviour is difficult and it is unclear whether a tailor-made online lifestyle advice is sufficient to change health behaviour and to maintain a healthy lifestyle.

## Introduction

Dementia is considered as a major public health concern.^1^ Due to the ageing population, the number of dementia cases will increase substantially in the next decades. In 2015, more than 46 million people worldwide were affected by dementia and this number is expected to increase to 131 million by 2050.^2^ This rise in people with dementia carries a high economic and social burden for society.^1^ In 2015, global costs of dementia reached 818 billion US dollars and will increase further.^3^ Currently, no curative treatments are available. Therefore, prevention is a key element to counteract the dementia epidemic.^4 5^

The most common types of dementia are Alzheimer’s disease (AD) (60%–70%), vascular dementia (VD) (15%–20%) or a combination of AD and VD (mixed dementia).^6–8^ The presence of a first-degree relative with AD doubles the risk for developing AD.^9^ This increased risk has several reasons. First, descendants of people with AD more often have a higher genetic predisposition for AD (eg, carrier of the apolipoprotein E (APOE) ε4 allele).^9^ Second, high blood pressure, vascular diseases and other vascular risk factors (ie, diabetes type 2, obesity, hypercholesterolemia) often cluster in families.^10^ Lastly, psychosocial behaviour runs in the family and also affects health behaviour and lifestyle.^11 12^ Not surprisingly, individuals with a parent who is recently diagnosed with AD or VD often worry about their own risk of developing dementia. Therefore, this life event (parental diagnosis of dementia) might encourage the willingness of individuals to change their health behaviour.^13^

Parental family history has been associated with an increased risk of dementia independently of known genetic risk factors.^9 14^ Therefore, a healthy lifestyle might be beneficial for individuals with a positive family history, especially for APOE ε4 carriers.^15–18^ Over the last decade, evidence of modifiable risk factors for dementia has been mounting.^4 6 19^ The Lancet commission on dementia prevention, intervention and care demonstrated that 35% of the dementia cases is attributable to modifiable risk factors (ie, less education, hearing loss, midlife hypertension, midlife obesity, smoking, depression, physical inactivity, social isolation and diabetes) and recommended to start interventions including more childhood education, promotion of physical exercise, reduction of smoking, maintaining social engagement and management of hypertension, diabetes, obesity, depression and hearing loss.^4 6 20^ Other major risk factors are hyperlipidaemia, coronary heart disease, renal dysfunction, Mediterranean diet and cognitive activity.^19^

Only a few studies examined the effectiveness of targeting these modifiable factors on cognitive decline and dementia incidence through a multidomain intervention, such as the Finnish Geriatric Intervention Study to Prevent Cognitive Impairment and Disability (FINGER) study,^21^ the Prevention of Dementia by Intensive Vascular care (PreDIVA) study^22^ and the The Multi-domain Alzheimer Preventive Trial (MAPT) study.^23^ These studies, with a follow-up varying from 2 to 6 years, found small or non-significant effects on cognition in older participants (eg, >60 years).^21–23^ Starting multidomain interventions earlier in life might be promising as cognitive decline begins already in midlife.^24 25^ However, since dementia is mainly prevalent in the elderly, a long follow-up period of approximately 20 years would be required in order to determine the effectiveness of interventions on dementia incidence.^24–26^ Furthermore, tailoring interventions improves the effectiveness of health behaviour change interventions.^27^ Web-based interventions have the potential to support health behaviour change as there is the opportunity to tailor lifestyle advice.^28–31^ They were especially effective when a theoretical basis or conceptual framework (eg, health belief model (HBM), transtheoretical model, theory of planned behaviour, I(integrated)-change model^32–36^), behaviour change techniques (eg, providing feedback on performance and information on the consequences of unhealthy behaviour) and several modes of delivery had been used.^27^

The first challenge of health behaviour change interventions is to achieve a high level of uptake for screening (eg, assessing risk and protective factors for dementia), reflecting the willingness to participate. A systematic review identified a large variation in uptake in health checks and lifestyle intervention programmes,^37^ depending on the type of recruitment strategy. The two main types of strategies for recruitment are the active and passive recruitment strategy. Active recruitment involves a personal invitation by the project staff and healthcare providers (eg, proactive) and passive recruitment involves recruitment of participants through various channels such as flyers and advertisements (eg, reactive).^38^ The most effective recruitment strategy is a proactive referral from a healthcare provider, while displaying posters and flyers showed to be less effective.^39 40^ Uptake also depends on other factors as described in social cognition models (eg, knowledge, perceived susceptibility and severity, facilitators, benefits and barriers and attitude towards such interventions).^32–36^ These factors are essential and useful to make a well-informed decision about dementia risk assessment, considering the possible benefits and harms. Therefore, information on dementia, the risk and protective factors for dementia, heritability and how to tackle risk and protective factors for dementia are important factors in the development of a web-based intervention. A previous study showed that the majority of the Dutch general population is unaware of the relationship between modifiable risk factors and brain health, particularly regarding major cardiovascular risk factors (eg, hypertension, hypercholesterolemia and coronary heart disease).^41^ It is shown that this lack of knowledge is a barrier to the uptake and maintenance of healthy behaviours for middle-aged individuals.^42^ Having a parent who is recently diagnosed with AD or VD could have led to an increased knowledge on dementia and risk perception.^13^ Therefore, middle-aged descendants of recently diagnosed people with AD or VD might be receptive to assess their risk and motivated to adopt a healthier lifestyle as they just realised their (familial) risk.^13 43^ Although we expect that the uptake in the active recruitment strategy will be higher compared with the passive recruitment strategy, participants recruited via the passive recruitment strategy might be more intrinsically motivated to adopt and maintain their healthy lifestyle and less likely to drop out of the study.

To our knowledge, none of the health behaviour intervention studies were aimed at a specific group of middle-aged adults with increased risk for dementia due to their parental family history of dementia. Therefore, this study aims to investigate the uptake and effectiveness of a tailor-made online lifestyle programme for dementia risk reduction (DRR) among middle-aged descendants of recently diagnosed (in the last 6 months) people with AD or VD in the Netherlands. This will give insight into what extent it is feasible to recruit middle-aged descendants of people with AD or VD at the memory clinics and whether these potential participants are willing to participate in a tailor-made online lifestyle programme in order to reduce their dementia risk.

## Methods and analysis

### Study setting and design

This study is a pragmatic cluster randomised controlled trial (RCT), including 21 participating memory clinics in the Netherlands who are randomly allocated to a passive or active recruitment of participants. Memory clinics allocated to the active recruitment strategy invite potential participants face-to-face by a member of the team of the memory clinic to participate in the tailor-made online lifestyle programme for DRR (also called the Demin study), next to posters and flyers that are placed in the waiting room of the memory clinic. Memory clinics allocated to the passive recruitment strategy, do not invite potential participants proactively, but invite potential participants to participate in the Demin study by posters and flyers that are placed in the waiting room of the memory clinic.

Patients with AD or VD (or their caregivers) receive an envelope either at the registration desk of the memory clinic or after the consult of the patient (only with active recruitment). This envelope is addressed to the middle-aged descendants of patients with recently diagnosed AD or VD and includes a patient information form (PIF) with information about the content of the study, the advantages and disadvantages of study participation and how potential participants can participate. Potential participants (one family member per patient) are asked to register themselves (eg, making an account) on the Demin website (www.demin.nl), by using the memory clinic specific login access code, which is reported on the front page of the PIF and represents the memory clinic in which the parent was diagnosed. The decision to participate is confirmed by the participants by signing the online informed consent form (electronic signature by using SMS-tan). After signing this form, individuals from both recruitment strategies are able to log in to their personalised website ‘My Demin’ and continue the intervention in an equal manner. The personalised website ‘My Demin’ is secured and only accessible for the participant by logging in with their personal email address, password and SMS-tan code. ‘My Demin’ contains the following information: (1) My personal (account) information, (2) Message inbox, (3) My online questionnaires, and (4) My personal health profile including online tailor-made lifestyle advice. After participants have completed the online questionnaire, they automatically receive a message with a request to make an appointment for physical examination including a fasting blood sample. Moreover, participants can invite siblings to participate in the study in ‘My Demin’.

The functionalities provided by the Demin website are based on the literature and input we received from people with a parent with dementia (focus group discussions).

### Randomisation of memory clinics

To prevent contamination between the two recruitment strategies, randomisation is performed at the level of the memory clinics. To enhance comparability between the intervention (participants of the active recruitment strategy) and control group (participants of the passive recruitment strategy), the memory clinics will be matched and randomised by a statistician, who is blind to the identity of the memory clinics and not involved in the study. First, all participating memory clinics will be matched into pairs based on the following criteria: (1) number of newly diagnosed dementia (VD, AD or mixed dementia) patients seen per year (range vary from 60 to 350 patients per year) and (2) the average social economic position (SEP) of the population living around the memory clinic (neighbourhood SEP), based on data from Statistics Netherlands.^44^ Second, the matched memory clinics will be randomised (pairwise randomisation) to an active recruitment strategy or passive recruitment strategy using a computer-generated random number list. As we expect a higher response rate in the active recruitment strategy group, we use an active:passive recruitment strategy ratio of 8:13 (see sample size calculations).

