### Sample size calculations

The primary outcome measure is uptake, which is defined as the percentage of eligible individuals that signed the online informed consent form and completed baseline assessment (online questionnaire and physical examination and a fasting blood sample). In order to detect a difference of 20% in uptake between the passive and active recruitment strategy (30% vs 50%), we need 94 participants in each group to achieve a power of 80% with alpha levels of 0.05 (total=188 participants). To take cluster randomisation into account, we use the formula 1+((n−1)*ICC) (inflation factor), where n is the average number of included participants per memory clinic and ICC is Intra Class Correlation.^45^ The ICC is unknown, but an ICC of 0.05 is a common value for cluster RCTs in hospitals.^46^ The estimated average of included participants per memory clinic per year is n=15 using a passive recruitment strategy and n=25 using an active recruitment strategy, taking into account non-response. With unequal cluster sizes, ‘n’ is replaced by ‘m’, where m is the sum of (M)^2^/sum(M) ((15^2^+25^2^)/(15+25)).^47^ This results in a sample size inflation factor of (1+((21.25–1)*0.05)=2.01. Therefore, the total number of participants needed is 378 (2.01*188). In order to recruit 378 participants, we need 21 memory clinics, of which eight memory clinics (responsible for 189 included participants) will be allocated to the active recruitment strategy and 13 memory clinics (responsible for 189 included participants) will be allocated to the passive recruitment strategy.

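### Randomising within matched pairs cannot produce the stated 8:13 allocation of 21 clinics; the two rules need to be reconciled

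*Protocol article*

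**What the plan says.** The section Study setting and design describes the trial as "including 21 participating memory clinics in the Netherlands who are randomly allocated to a passive or active recruitment of participants".

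The section Randomisation of memory clinics then gives the mechanism in two steps. First, "all participating memory clinics will be matched into pairs based on the following criteria"; the criteria are the yearly number of newly diagnosed dementia patients (60 to 350 across clinics) and neighbourhood SEP. Second, "the matched memory clinics will be randomised (pairwise randomisation) to an active recruitment strategy or passive recruitment strategy", using a computer-generated list. The stated aim of matching is comparability between the arms. The statistician who matches and randomises is not involved in the study and does not know which clinic is which.

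The same paragraph ends with the statement that "we use an active:passive recruitment strategy ratio of 8:13", because a higher response is expected with active recruitment. The section Sample size calculations derives the eight and the 13. The article does not mention triplets, matched sets of unequal size, strata, or a rule for clinics that fall outside a pair.

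**The concern.** Pairwise randomisation normally sends one member of each pair to each arm, so it produces equal arms. An odd number of clinics and an 8:13 ratio are both incompatible with that. This is a conflict between two statements in one paragraph, and fuller detail elsewhere could not make both true.

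The primary outcome is a between-clinic comparison of uptake with only 21 clusters, so the way clinics reach their arms carries much of the weight of the conclusion. Clinic volume varies almost sixfold (350/60 = 5.8), and new cases also form the denominator of uptake. A reader cannot tell which clinics were matched across arms, or how those without an opposite-arm partner were assigned.

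**Working it through.** **Inputs, all from the protocol article.** 21 clinics (Study setting and design). Pairs, pairwise randomisation and 8:13 (Randomisation of memory clinics). Uptake 30% vs 50%, power 80%, alpha 0.05, 94 per group, ICC 0.05, 15 participants per passive clinic and 25 per active clinic, 189 participants per arm (Sample size calculations).

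**Step 1: reproduce the plan's own figures.**
- Two proportions, two-sided 0.05 (sidedness is not stated): n = [1.96·√(2·0.4·0.6) + 0.8416·√(0.3·0.7 + 0.5·0.5)]² / 0.20² = 93 per group. The plan has 94, which is close enough.
- Weighted cluster size: (15² + 25²)/(15 + 25) = 850/40 = 21.25.
- Inflation: 1 + (21.25 − 1)·0.05 = 2.0125.
- Total: 188 × 2.0125 = 378.35; the plan has 378, or 189 per arm.
- Active clinics: 189/25 = 7.56, rounded up to 8. Passive clinics: 189/15 = 12.6, rounded up to 13. Sum 21.

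The 8:13 ratio therefore follows from the plan's own inputs. The sample size arithmetic is not at fault.

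**Step 2: what the stated randomisation can produce.** 21 = 2 × 10 + 1. Ten pairs give 10 active and 10 passive clinics, and the remaining clinic goes to one arm or the other. The possible splits are 10:11 and 11:10. Eight to 13 is not among them.

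**Step 3: what 8:13 implies if every matched set is a pair.** Let d be the number of pairs with one active and one passive clinic. Each uses one active clinic, so d ≤ 8. Passive clinics without an active partner number 13 − d ≥ 13 − 8 = 5. That is at least 5/13 = 38% of the passive arm and 5/21 = 24% of all clinics. Such clinics could be paired with each other, but a pair that lies wholly in the passive arm gives no between-arm contrast.

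**Step 4: can 8:13 be reached with every clinic in a randomised set?** Yes, if sets may differ in size. Let p be the number of pairs (1 active, 1 passive) and t the number of triplets (1 active, 2 passive). Then p + t = 8 and p + 2t = 13, so t = 5 and p = 3. Check: 3 × 2 + 5 × 3 = 21 clinics. With one active and one or two passive clinics per set, this is the only solution.

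**Step 5: would it be simpler to drop the ratio?** At the plan's yields, 10:11 gives 10 × 25 = 250 active and 11 × 15 = 165 passive participants, and 11:10 gives 275 and 150. In both cases the passive arm falls short of 189. At 8:13 the yields are 200 and 195. Keeping the ratio and changing the randomisation rule fits the plan better.

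**The case against.** The best defence is that a condensed article may use the word pairs loosely for matched sets. Mixed sets of two and three clinics deliver 8:13 exactly, with every clinic randomised. So it would be wrong to say that 8:13 can arise only with five unpaired clinics; the count of five holds for strict pairs. The defence shows that a workable procedure exists, but the article does not describe one, and its text says pairs twice.

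A reader might go further and infer that five clinics were simply put in the passive arm, so that the primary comparison is partly non-randomised. The documents do not support that. The article says the 21 clinics are randomly allocated, by an uninvolved statistician blind to clinic identity. If surplus clinics were drawn at random, randomisation is intact and only their matching is lost. Lost matching also makes imbalance possible, not certain.

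The planned primary analysis is a multilevel logistic regression with clustering by clinic. It does not depend on pairs, so an unpaired clinic is not lost from the model. This point stands, and it limits the harm.

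A reader might also infer that 8:13 is a poor ratio because near-equal arms estimate uptake more precisely. The plan's yields imply 50 eligible people per clinic in either arm (15/0.30 and 25/0.50) and a design effect of 1 + 49·0.05 = 3.45. The variance of the uptake difference is then 3.45/50 × (0.25/8 + 0.21/13) = 0.00327 at 8:13, and 3.45/50 × (0.25/10 + 0.21/11) = 0.00304 at 10:11. That is about 7% less, with power about 94% and 95%, both well above 80%. Similar enrolment in the arms also serves the planned between-arm comparisons of LIBRA score, risk factors and health beliefs. This is a reasonable trade-off and no fault.

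**Conclusion.** The concern holds as a contradiction in the allocation rule. With pairwise randomisation in its usual sense (one clinic of each pair to each arm), 21 clinics can split only 10:11 or 11:10. With strict pairs, the stated 8:13 leaves at least five of 13 passive clinics without an active partner, and the intended matching on volume and SEP is lost for them. These counts are exact and need no assumption about uptake or ICC. They count clinics without a partner and do not measure bias.

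Any loss of randomisation is conditional on surplus clinics having been assigned without a random draw, which the article does not state. The ratio, the sample size and the planned model are unaffected. This should be fixed, because the procedure for the primary comparison cannot be carried out as written. It is not grave enough to block the trial.

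**What to change.** Keep 8:13 and replace the pairwise rule with one that can deliver it. Either of these works:
- Form five matched triplets, randomised one active to two passive, and three matched pairs, randomised one to one.
- Use covariate-constrained randomisation: draw 8 active clinics from the C(21,8) = 203,490 possible allocations, restricted to those balanced on yearly new diagnoses and neighbourhood SEP.

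If allocation is already done, describe what was done: which matched sets were formed, and how the clinics outside an active/passive pair were assigned. Only if those clinics were not randomised, add a sensitivity analysis of uptake restricted to the randomised pairs.

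The cost is one paragraph and a new randomisation program if allocation is still to come, or a short disclosure if it is not. No extra clinics or participants are needed.
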